### Sample size considerations

Recent data showed that patients treated by AS have a mean diameter reduction of 29.7 ± 19.76% after four weeks [23]. By adding pasireotide, we want to establish a decrease in cyst diameter of 50% after four weeks. A sample size of 15 patients per arm, leading to a total of 30 patients, is required to be able to obtain a significant difference between the two groups (power: 80%; α: 0.05). Taking into account the possibility of 10% protocol violators and/or dropouts, we aim to include 17 subjects per arm, giving a total of 34 patients.

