### Statistical analysis

Intention-to-treat (ITT) analyses will be used for all clinical outcome variables. The ITT sample includes all patients who received at least one dose of study medication. In addition, we will carry out a parallel analysis on the per-protocol treated population. This sample is defined as all patients who have received both injections, AS and all ultrasound measurements. The primary outcome of this study is the proportional (%) change in cyst diameter of the treated hepatic cyst four weeks after AS, as measured by ultrasound. The mean diameter of each orthogonal diameter measured by the blinded primary investigator will be used for analysis. Subsequently, we will calculate a mean diameter from the three mean orthogonal diameters. Proportional change will be calculated by dividing the reduction of mean cyst diameter at four weeks by mean cyst diameter at baseline, multiplied by 100. Depending on distribution, values will be presented as mean ± SD or as median ± interquartile range. Consequently, differences between the treatment and placebo arm will be calculated using the independent student’s t-test or the Mann-Whitney U test, respectively. Absolute reduction and volume reduction will be presented and analyzed similar to data for the primary endpoint. Cyst recurrence will be compared between both groups using Fisher’s exact test. The cyst diameter measurements from the second blinded investigator will be used as a control to evaluate intra- and interobserver variability by performing a Bland-Altman analysis. Symptoms of the GIS-questionnaire will be dichotomized (0 to oneversus two to six) and compared between the treatment and placebo arm using the chi-square test. Health-related quality of life domain scores and component scores (SF-36) will be compared between both arms using the Mann-Whitney U test. Frequency tables will be compiled for (serious) adverse events classified according to the standard World Health Organization - Adverse Reaction Terminology (WHO-ART) Body System Dictionary and preferred terms. All statistical analyses will be two-sided, with a critical significance level of 5%.

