In the context of this study we want to evaluate whether these inhibitory mechanisms of somatostatin analogues can halt cyst fluid re-accumulation following AS. We have chosen to apply the multi-receptor-targeted, long-acting somatostatin analogue pasireotide (SOM230) [16]. This cyclohexapeptide has a high binding affinity to SSTR 1, 2, 3 and 5 which are all expressed on cholangiocytes [12]. Compared to conventional somatostatin analogues, pasireotide has a broader binding profile and a higher affinity to SSTR 1, 3 and 5. In a polycystic kidney disease rodent model pasireotide decreased intracellular cAMP, cholangiocyte proliferation and expansion of hepatic cysts more effectively than octreotide [17]. Pasireotide is approved in the European Union and United States for the treatment of Cushing’s disease, and is currently being investigated for treatment of other diseases such as acromegaly and neuroendocrine tumors. Two formulations of pasireotide are available: an immediate release and a one-month depot formulation. To ensure adequate pasireotide levels and optimize patient adherence, we have chosen to administer the LAR formulation of pasireotide. A previous pharmacokinetic study of pasireotide LAR in healthy volunteers showed that pasireotide levels reached a peak (*t*_max_) around 20 days following administration [18]. Therefore, to secure adequate levels subsequent to AS, a first injection will be administered two weeks prior to AS, followed by a second injection two weeks following AS.

The strength of this study is its design: a randomized, double-blind, placebo-controlled trial. This will minimize confounding of results. Further, this study is powered on a clinical relevant difference of 50% in the pasireotide arm compared to the expected 30% cyst diameter reduction in the control arm. We believe that a statistical significant finding will have direct implications for future AS treatment. Smaller differences between arms will not be detected in view of power issues. Nevertheless, given the additional costs and potential side effects of pasireotide, we believe that a strong improvement over conventional AS is needed to justify the implementation of this combination treatment. Finally, with this study we hope to achieve a better understanding in the pathological mechanisms behind hepatic cyst development and fluid re-accumulation following AS.

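### Fifteen per arm gives about 78% power, not 80%, with the planned t-test, and the 10% allowance does not fully offset violators kept in the ITT analysis

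*Protocol article*

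**What the plan says.** The protocol article, under Sample size considerations, takes its control-arm figures from earlier data: "patients treated by AS have a mean diameter reduction of 29.7 ± 19.76% after four weeks". The target for the active arm is 50%: "By adding pasireotide, we want to establish a decrease in cyst diameter of 50% after four weeks". From these it concludes "A sample size of 15 patients per arm, leading to a total of 30 patients, is required", with "power: 80%; α: 0.05". It then inflates: "Taking into account the possibility of 10% protocol violators and/or dropouts, we aim to include 17 subjects per arm", which makes 34 in total. It names no sample size formula and gives no SD for the pasireotide arm.

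Under Statistical analysis, the primary comparison is an independent Student's t-test, or a Mann-Whitney U test if the distribution calls for it, and "All statistical analyses will be two-sided, with a critical significance level of 5" per cent. ITT is used for all clinical outcomes, and the ITT set contains everyone given at least one dose of study medication. A parallel per-protocol analysis is limited to patients with both injections, the sclerotherapy procedure and every ultrasound measurement.

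**The concern.** There are two mismatches between how the sample size was derived and how the trial will be analysed.

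- **Formula and test.** Fifteen per arm is what one obtains by treating the SD as known. The t-test estimates it from 28 degrees of freedom, which costs a noticeable amount of power at this size.
- **Allowance and analysis set.** Dividing by 0.9 is right for patients who leave the analysis. A protocol violator who has had one dose stays in the ITT set. That patient does not reduce n, but may pull the active-arm mean towards control, and dividing by 0.9 is not designed to correct for that.

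Both bear on how a non-significant primary result would be read. The Discussion relies on the power statement when it accepts that smaller differences will go undetected. If the true power is a few points below the stated 80%, a null result is slightly weaker evidence against a 20-point benefit than readers will be told.

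**Working it through.** **Inputs.** From Sample size considerations: control mean 29.7, active mean 50, SD 19.76, α 0.05, power 80%, allowance 10%. From Statistical analysis: two-sided testing, t-test. From Randomization and treatment allocation: 1:1. Assumption: the SD of 19.76 applies to both arms.

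**Step 1: reproduce the plan's figure.**
- Difference: 50 − 29.7 = 20.3 points. Standardised: d = 20.3/19.76 = 1.027.
- Normal approximation: n = 2(1.960 + 0.842)²/d² = 14.87, rounded up to 15 per arm.
- Normal-approximation power at 15 per arm: 80.3%.
- Inflation: 15/0.9 = 16.7, rounded up to 17 per arm, 34 in total.

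Both stated figures reproduce. A one-sided calculation would give 12 per arm, so it is not the source.

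**Step 2: power of the planned test.** For the two-sided t-test, power comes from the noncentral t distribution with 2n − 2 degrees of freedom and noncentrality d√(n/2). At n = 15 the noncentrality is 1.027 × √7.5 = 2.81.

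| Analysed per arm | Normal approximation | t-test |
|---|---|---|
| 15 | 80.3% | 77.5% |
| 16 | 82.8% | 80.3% |
| 17 | 85.0% | 82.7% |

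Solving for 80% gives 15.89, so 16 per arm. With the same 10% allowance, 16/0.9 = 17.8, so 18 per arm or 36 in total, against the planned 34. At exactly 10% loss from 17 per arm (17 × 0.9 = 15.3), t-test power is about 78.4%. With 15 per arm, the difference detectable with 80% power is about 20.9 points instead of 20.3.

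**Step 3: violators kept in the ITT set.** The documents do not say how many violators to expect or how much effect they would lose, so this step is illustrative. Assume that a fraction v of the active arm responds like controls and that nobody is lost. The mean difference becomes (1 − v) × 20.3: 19.3 points at v = 5% and 18.3 points at v = 10%. In the last column the active-arm variance grows by v(1 − v) × 20.3², because that arm is then a mixture.

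| Per arm | v | Power, SD 19.76 | Power, SD widened by the mixture |
|---|---|---|---|
| 15 | 10% | 68.6% | 66.6% |
| 17 | 5% | 78.8% | 77.8% |
| 17 | 10% | 74.3% | 72.4% |

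At v = 10%, going from 15 to 17 per arm recovers about 6 points (68.6% to 74.3%) but does not restore 80%.

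**The case against.** The strongest reply is that nothing was miscalculated. The normal approximation is a standard formula, the article claims no other, and its inputs lead to 15 and then 17. The refinement is one patient per arm and about 2.5 power points. The trial randomises 17 per arm, not 15, and power is above 80% if 16 or 17 per arm are analysed. The 77.5% applies only if two of 17 are lost in each arm, which is 11.8% and slightly more than the planned 10%. All of this stands, and it sets the size of the point. It does not rescue the statement as printed, which attaches 80% to 15 per arm in a trial that will use a t-test.

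On the allowance, it can fairly be said that the 10% also covers dropouts, for whom the inflation works, that it preserves n for the per-protocol analysis, and that it raises ITT power even under dilution. A violator need not lose all benefit either. Someone who does not get the second injection has still had a one-month depot dose two weeks before the procedure. These points stand too. A reader might infer that the inflation gives the ITT analysis no protection. The documents do not support that. The protection is partial.

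Two further readings are tempting and should not be pressed. The Discussion says "this study is powered on a clinical relevant difference of 50% in the pasireotide arm compared to the expected 30% cyst diameter reduction", and recomputing with 30% would lower the power further. That figure is evidently 29.7 rounded in narrative, and the calculation itself is in the sample size section. A lower power could also be quoted for the Mann-Whitney test by assuming normal data, but with normal data the plan would use the t-test.

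**Conclusion.** The point holds as a small correction. The stated 80% at 15 per arm is right under the normal approximation and slightly too high for the planned two-sided t-test, whose power is 77.5%. Eighty per cent needs 16 per arm. With the 34 patients planned, power runs from about 78% at the allowed 10% loss to 82.7% with none. A reader might infer an arithmetic error or a materially underpowered trial. Neither follows from the documents.

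The mismatch between the allowance and the ITT set is correct in principle. Its size is unknown: 79% or 74% at 17 per arm are scenarios for 5% or 10% of active patients gaining nothing with nobody lost, and not forecasts. All t-test figures assume a common SD of 19.76 and approximately normal data.

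**What to change.** Keep 34 patients and change the wording of the sample size section.

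1. Say that 15 per arm comes from the normal approximation and that a common SD of 19.76 is assumed.
2. State t-test power for 29.7% against 50% as about 78% with 15 evaluable per arm and about 83% if all 17 per arm are analysed.
3. Say that the 10% allowance compensates for loss of n only, and that violators who remain in the ITT set act through a smaller effect.
4. If a power under ITT dilution is given, label it as an assumption and show a range: for example, at 17 per arm with nobody lost, 79% if 5% of the active arm respond like controls and 74% if 10% do.

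Recruitment, conduct and analysis are unaffected. The only cost is that the printed power is slightly less favourable.

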### Statistical analysis

Intention-to-treat (ITT) analyses will be used for all clinical outcome variables. The ITT sample includes all patients who received at least one dose of study medication. In addition, we will carry out a parallel analysis on the per-protocol treated population. This sample is defined as all patients who have received both injections, AS and all ultrasound measurements. The primary outcome of this study is the proportional (%) change in cyst diameter of the treated hepatic cyst four weeks after AS, as measured by ultrasound. The mean diameter of each orthogonal diameter measured by the blinded primary investigator will be used for analysis. Subsequently, we will calculate a mean diameter from the three mean orthogonal diameters. Proportional change will be calculated by dividing the reduction of mean cyst diameter at four weeks by mean cyst diameter at baseline, multiplied by 100. Depending on distribution, values will be presented as mean ± SD or as median ± interquartile range. Consequently, differences between the treatment and placebo arm will be calculated using the independent student’s t-test or the Mann-Whitney U test, respectively. Absolute reduction and volume reduction will be presented and analyzed similar to data for the primary endpoint. Cyst recurrence will be compared between both groups using Fisher’s exact test. The cyst diameter measurements from the second blinded investigator will be used as a control to evaluate intra- and interobserver variability by performing a Bland-Altman analysis. Symptoms of the GIS-questionnaire will be dichotomized (0 to oneversus two to six) and compared between the treatment and placebo arm using the chi-square test. Health-related quality of life domain scores and component scores (SF-36) will be compared between both arms using the Mann-Whitney U test. Frequency tables will be compiled for (serious) adverse events classified according to the standard World Health Organization - Adverse Reaction Terminology (WHO-ART) Body System Dictionary and preferred terms. All statistical analyses will be two-sided, with a critical significance level of 5%.

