### Ultrasound measurements

The blinded primary investigator will perform cyst diameter measurements by ultrasonography. The treated hepatic cyst will be visualized in two planes to measure each maximal orthogonal diameter (craniocaudal, anteroposterior and mediolateral) three times. As a secondary endpoint, cyst volume will be estimated by multiplying the maximum of each orthogonal diameter by 0.523 [10]. The measurement will be performed using a 3.5 MHz convex transducer (Acuson X150™, Siemens Healthcare, Erlangen, Germany). A blinded independent investigator will repeat all measurements. Both investigators are trained and experienced in measuring hepatic cyst diameter.

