This study has several limitations. First, the effect of treatment will be measured by ultrasonography. Since we will perform cyst measurements within short intervals we have selected ultrasonography as the most appropriate imaging modality to avoid exposure to radiation (from computed tomography scans) and high costs (from magnetic resonance imaging). However, ultrasound measurements are operator-dependent and are therefore susceptible to bias. To minimize biased results, we have added several safety measures. All measurements will be performed according to standard operating procedures and will be executed in triplicate. Moreover, all measurements will be performed by the same investigator who is blinded for treatment allocation. In addition, a second, blinded independent investigator will repeat all measurements. Second, in this study sclerotherapy will be performed with 100% ethanol. Multiple sclerosing agents are in use for AS ranging from ethanol to tetracycline antibiotics, polidocanol, ethanolamine oleate or hypertonic saline [8,28-32]. This might limit the generalization of our findings. On the other hand, ethanol is cheap, widely available and the clinical experience with this agent is large. Finally, AS will be performed by a number of interventional radiologists, theoretically introducing performance bias. Nevertheless, AS is a protocol procedure and large differences in treatment outcome between interventional radiologists are not to be expected.

To summarize, the SCLEROCYST trial is designed to evaluate the additional effect of a somatostatin analogue combined with AS. We aim to reduce fluid re-accumulation following treatment leading to increased cyst diameter reduction and symptomatic relief.

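### Free improvement (minor): two blinded readers measure every cyst but only one feeds the primary endpoint, and the maximum used for volume is ambiguous and differs from the mean used for diameter

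*Protocol article*

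**What the plan says.** The Ultrasound measurements section has the blinded primary investigator "measure each maximal orthogonal diameter (craniocaudal, anteroposterior and mediolateral) three times". It adds: "A blinded independent investigator will repeat all measurements".

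The Statistical analysis section takes the primary endpoint from one of the two: "The mean diameter of each orthogonal diameter measured by the blinded primary investigator will be used for analysis". The three mean orthogonal diameters are then averaged, and percentage change is taken from baseline. The other reader's data have a different purpose: "The cyst diameter measurements from the second blinded investigator will be used as a control to evaluate intra- and interobserver variability", by Bland-Altman analysis.

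The Discussion concedes that "ultrasound measurements are operator-dependent and are therefore susceptible to bias". It offers three safeguards: triplicate readings, one constant reader ("all measurements will be performed by the same investigator who is blinded for treatment allocation") and the blinded repeat by a second investigator.

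For the secondary volume endpoint, the Ultrasound measurements section says "cyst volume will be estimated by multiplying the maximum of each orthogonal diameter by 0.523". The Statistical analysis section says only that volume reduction is handled like the primary endpoint.

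**The concern.** There are two separate points.

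**Unused second reader.** The article lists the second blinded reader among its measures against operator-dependent error. A Bland-Altman analysis describes disagreement between readers but does not reduce it, and the readings do not enter the endpoint. Averaging two readers would halve the part of reader error that is independent between them, using data the trial collects anyway. With 34 patients, even a modest gain in precision is worth having.

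**Volume rule.** Diameter uses the mean of three readings and volume uses a maximum, with no reason given. The word can be read in two ways. The same section already calls each orthogonal diameter maximal, so the maximum may be the largest extent in each direction. It may also be the largest of the three readings. The second reading inflates every diameter. The inflation is proportionally greater in the smaller cyst after treatment, so percentage volume reduction is understated, and a maximum is noisier than a mean.

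**Working it through.** **1. The plan's own sample size**

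Inputs from Sample size considerations: control "mean diameter reduction of 29.7 ± 19.76% after four weeks", target 50%, power 80%, α 0.05 (two-sided, from Statistical analysis).

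- Difference: 50 − 29.7 = 20.3 points.
- Normal approximation: n = 2 × (1.960 + 0.842)² × 19.76² / 20.3² = 14.9, so 15 per arm.
- Dropout: 15 / 0.9 = 16.7, so 17 per arm and 34 in total.

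The stated figures reproduce. Exact t-test power is 77.5% at 15 per arm and 82.7% at 17 per arm.

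**2. Averaging two readers**

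Let f be the share of outcome variance due to reader error that is independent between readers. The article gives no value, so f is assumed. Averaging two readers halves that part: SD = 19.76 × √(1 − f/2).

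| f (assumed) | SD | power, 17 per arm |
|---|---|---|
| 0 (reference: 82.7% is also the single-reader power) | 19.76 | 82.7% |
| 2% | 19.66 | 83.1% |
| 5% | 19.51 | 83.7% |
| 10% | 19.26 | 84.6% |
| 30% | 18.22 | 88.3% |

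To relate f to centimetres, let e be the SD of one reader's error in the mean diameter. For baseline D₀ and true reduction r, the error variance of the percentage change is about (100/D₀)² × e² × (1 + (1 − r)²). With r = 29.7%:

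- D₀ = 10 cm, e = 0.3 cm: error SD 3.67 points, f = 3.67² / 19.76² = 3.4%.
- D₀ = 6 cm, e = 0.3 cm: error SD 6.11 points, f = 9.6%.
- D₀ = 10 cm, e = 0.1 cm: error SD 1.22 points, f = 0.4%.

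A range of 2 to 10% is therefore plausible but not documented, and f may be lower.

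**3. Volume: largest of three readings against their mean**

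The factor 0.523 is π/6 = 0.5236, the ellipsoid factor applied to the product of three diameters. It cancels in a percentage change.

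For three independent normal readings, the expected maximum exceeds the true value by 0.846 reading SDs. The apparent volume reduction is then about 1 − [((1 − r)D₀ + 0.846s) / (D₀ + 0.846s)]³, where s is the assumed reading SD. The true values are 1 − 0.703³ = 65.26% (control) and 1 − 0.5³ = 87.50% (active), a difference of 22.24 points.

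| D₀ | s | control reads (loss) | active reads (loss) | arm difference |
|---|---|---|---|---|
| 10 cm | 0.2 cm | 64.52 (0.74) | 86.87 (0.63) | 22.35 |
| 10 cm | 0.4 cm | 63.80 (1.46) | 86.23 (1.27) | 22.43 |
| 6 cm | 0.2 cm | 64.03 (1.22) | 86.44 (1.06) | 22.41 |
| 6 cm | 0.4 cm | 62.85 (2.41) | 85.39 (2.11) | 22.54 |

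Simulation (200,000 draws per scenario) agrees. Over these four scenarios the maximum reads 0.6 to 2.5 points below the mean-based volume reduction. At 10 cm and s = 0.2 cm in the active arm, for example, it gives 86.86% against 87.50%. At 6 cm and s = 0.4 cm in the control arm it gives 62.60% against 65.10%.

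Measurement-error SD is about 30% larger in the control arm (1.56 against 1.21 points at 10 cm, s = 0.2 cm) and 32 to 38% larger in the active arm. Over a wider range of s, 0.1 to 0.5 cm, the simulated arm difference runs from 22.30 to 22.81 points, so it moves by at most 22.81 − 22.24 = 0.57.

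**The case against.** **The single reader is a legitimate choice.** One constant blinded reader with averaged triplicates, plus a second reader for reliability, is coherent and prespecified. The SD of 19.76 is an observed SD and should already contain measurement error, so using one reader does not undermine the planned power. This stands, and the point is therefore an improvement and not an error.

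**The gain may be smaller still.** The primary endpoint averages nine readings. If all nine errors were independent with a reading SD of 0.4 cm on a 10 cm cyst, reader error would be about 1.5 to 1.6 percentage points, or 0.6 to 0.7% of the variance, and the gain about 0.1 power point. A 2 to 10% share needs error that persists across one reader's repeats. That is plausible with ultrasound but not documented.

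**Stronger readings that the article does not support:**

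- *The primary comparison is biased.* The reader is blinded and the same for all patients. A proportional reader error cancels in a percentage change, and a constant offset acts on both arms: +0.2 cm on a 10 cm cyst gives 29.1% and 49.0% in place of 29.7% and 50%. One might suspect that glucose values and adverse events reveal the allocation to the reader. The article assigns adverse-event documentation at follow-up to the researcher and does not say that this person performs the scans.
- *The volume rule hides more benefit in the better arm.* The loss is smaller in the active arm (1.27 against 1.46 points at 10 cm, 0.4 cm), and the arm difference widens slightly.
- *The trial is planned with under 80% power.* The 77.5% is the exact t-test figure at 15 evaluable per arm. At the planned 17 it is 82.7%, and the stated number reproduces by the usual formula.
- *The maximum is certainly the largest reading.* The wording also permits the largest extent, in which case the calculated understatement does not arise. The ambiguity remains.

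**Conclusion.** The point holds as a minor, cost-free improvement.

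The second reader's data could tighten the primary endpoint by about 0.4 to 2 power points at 17 per arm (82.7% to between 83.1% and 84.6%) if independent reader error makes up 2 to 10% of outcome variance. That share is assumed, and a smaller share gives less.

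The volume rule is the firmer part, because it can be read in two ways and differs without explanation from the rule for diameter. If it means the largest of three readings, each arm's reported volume reduction is too low by roughly 0.6 to 2.5 points and has about 30% more measurement-error SD. This assumes independent normal reading errors with SD 0.2 to 0.4 cm and baseline cysts of 6 to 10 cm. The between-arm difference moves by under 0.6 points, so the conclusion on treatment effect would hardly change. What is affected is the reported size of reduction on a secondary endpoint.

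**What to change.** Make these changes before unblinding:

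1. **Volume.** State it as 0.523 × the product of the three mean orthogonal diameters, so that it rests on the same triplicate means as the diameter endpoint. This removes the ambiguity.
2. **Diameter.** Prespecify the average of the two blinded readers' triplicate means at every visit, baseline included. Where one reader's measurement is missing, use the reader who is available. Keep the primary investigator alone as a sensitivity analysis.
3. **Agreement.** Keep the Bland-Altman analysis as reporting on measurement reliability.

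The cost is a change of wording in the Ultrasound measurements and Statistical analysis sections. No extra scan, reader, visit or patient is needed.

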## Methods/Design

### Study aim

The primary objective of the SCLEROCYST trial is to evaluate the combined effect of AS and pasireotide on cyst diameter reduction. Secondary objectives are to determine symptomatic relief and cyst recurrence.

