#### Secondary outcome

Secondary outcomes are mean proportional change (%) in cyst diameter two, 12 and 24 weeks after AS. Moreover, proportional change (%) in volume, absolute diameter reduction (cm) and rate of cyst recurrence (>80% of original diameter) at follow-up visits will be assessed. In addition, symptoms and health-related quality of life will be measured at baseline, four, 12 and 24 weeks after AS. Finally, any complications or adverse events reported during procedure or follow-up visits will be recorded.

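### Symptom relief is tested on GIS items cut at 0–1 versus 2–6, with no stated use of baseline for GIS or SF-36; the cut does not measure relief and costs power

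*Protocol article*

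**What the plan says.** Under Study aim: "Secondary objectives are to determine symptomatic relief and cyst recurrence". The abstract likewise lists relief of symptoms and improvement in quality of life among the secondary outcomes.

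Under Secondary outcome, "symptoms and health-related quality of life will be measured at baseline, four, 12 and 24 weeks after AS". The Screening visit section confirms that the GIS and SF-36 are completed before treatment. Patient-reported outcome measures describes the GIS as 11 symptoms, each scored 0 to 6, and the SF-36 as eight domain scores and two component scores.

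Under Statistical analysis, the GIS rule is "Symptoms of the GIS-questionnaire will be dichotomized (0 to oneversus two to six"), followed by a chi-square test between arms. For the SF-36, "Health-related quality of life domain scores and component scores (SF-36) will be compared between both arms using the Mann-Whitney U test". The same section expresses the cyst-diameter outcome relative to baseline and uses Fisher's exact test for recurrence. Finally, "All statistical analyses will be two-sided, with a critical significance level of 5" per cent.

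**The concern.** Relief is a change from where the patient started. The GIS rule sorts each patient by score at a visit and ignores the starting score, although that score is on file. It also reduces seven ordered levels to two.

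Both choices discard information in a trial sized for cyst diameter alone. Real relief could go undetected because patients improve without crossing the cut. Chance baseline differences between two small arms would stay in the comparison. The article fixes this method itself, so it is not a detail left to an unseen analysis plan.

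**Working it through.** **1. The plan's own figure.** Inputs from Sample size considerations: "patients treated by AS have a mean diameter reduction of 29.7 ± 19.76% after four weeks"; "we want to establish a decrease in cyst diameter of 50% after four weeks"; "power: 80%; α: 0.05".

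n per arm = 2(z₀.₉₇₅ + z₀.₈₀)²(SD/Δ)² = 2(1.960 + 0.842)²(19.76/20.3)² = 14.9, so 15. Then 15/0.9 = 16.7, so 17 per arm and 34 in total. The stated size reproduces (the noncentral t gives 77.5% power at 15 and 82.7% at 17). It concerns diameter only; no power is stated for GIS or SF-36.

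**2. What the cut counts.**

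| Item score, baseline → visit | Change | Category at visit |
|---|---|---|
| 6 → 2 | −4 | symptomatic |
| 2 → 1 | −1 | good result |
| 0 → 0 | 0 | good result |

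The last row is realistic. Eligibility requires a symptomatic cyst, not the presence of each of 11 symptoms.

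**3. Power of chi-square on one cut item** (exact enumeration of all 2×2 tables; the proportions scoring 2 or more are assumptions).

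| Control v active | 15 per arm | 17 per arm |
|---|---|---|
| 50% v 30% | 19.5% | 23.0% |
| 60% v 30% | 37% | 45% |
| 60% v 20% | 63% | 70% |

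For 80% power, a control proportion of 60% must fall to about 13% (15 per arm) or 15% (17 per arm). The usual two-proportion formula asks for 42 per arm for 60% v 30%, and 93 for 50% v 30%.

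**4. Cost of the cut and of leaving out baseline, GIS item** (simulation; score distributions and baseline correlations are assumptions).

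Set A: rounded 0–6 scores, SD 1.5, true difference 1.5, 15 per arm, baseline correlation 0.5. The share scoring 2 or more is Φ((mean − 1.5)/1.5).

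| Means, control/active | Share ≥2 | Chi-square on cut | Mann-Whitney, full scale | ANCOVA with baseline |
|---|---|---|---|---|
| 3.0/1.5 | 84% v 50% | 54% | 70% | 80% |
| 4.0/2.5 | 95% v 75% | 33% | 72% | 83% |

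The cut costs 70 − 54 = 16 points in the first row and 72 − 33 = 39 in the second. Baseline adds 10 and 11 more. With means 2.5/1.3 (an effect of 0.8 SD), the cut costs about 12 points.

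Set B: effect 0.8 SD, 60% of controls scoring 2 or more. ANCOVA is shown for correlations 0.3/0.5/0.7.

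| Per arm | Chi-square on cut | Mann-Whitney, full scale | ANCOVA with baseline |
|---|---|---|---|
| 15 | 38–40% | about 49% | 52/57/64% |
| 17 | 45–49% | about 54% | 56/61/69% |

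Chi-square does not depend on the correlation, so its spread is simulation error. Across this set, and the same set at 1 SD, the cut costs 5–12 points. At 0.8 SD, baseline adds from 56 − 54 = 2 to 64 − 49 = 15 points.

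**5. SF-36** (effect 0.8 SD assumed). Mann-Whitney on follow-up scores has about 53% power at 15 per arm and 59% at 17. ANCOVA with baseline has 60/69/84% and 66/74/89% for correlations 0.3/0.5/0.7. About 3 points of the gap at 15 per arm come from Mann-Whitney rather than a t-test (53% v 56%).

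If change scores are meant, adjustment still helps. With equal variances, the ANCOVA residual variance divided by the change-score variance is (1 − ρ²)/(2(1 − ρ)) = (1 + ρ)/2, which is 0.65, 0.75 and 0.85 at those correlations.

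**6. Type I error and sparseness.** Exact chi-square type I error at 15–17 per arm runs from 0.5% (5% prevalence) to 5.8%. An expected count falls below 5 only when pooled prevalence is below 33% or above 67% (15 per arm), or below 29% or above 71% (17 per arm). In Set A, Fisher's exact test has 35% and 18% power, against 54% and 33% for chi-square.

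**The case against.** The strongest reply is that comparing arms at follow-up is valid under randomisation. Patients never troubled by a symptom are expected equally in both arms, so they dilute the comparison but do not bias it. These are secondary outcomes, and much of the low power comes from 15–17 patients per arm, which no analysis wording repairs. All of that stands. The cut and the unused baseline are the avoidable part.

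The size of the loss also depends on assumed scores. The 39-point figure needs a full 1-SD effect and a cut well below where most patients score. That stands too, which is why a range is given.

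Several stronger readings are tempting but unsupported:

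- A reader might infer that sparse tables make chi-square invalid. The article gives no item prevalences, mid-range items are not sparse, and the error rate stays at or below 5.8%. Fisher for recurrence and chi-square for GIS is an inconsistency of style.
- A reader might take the SF-36 test to use follow-up scores. The text says only domain and component scores, so change scores are not excluded. The GIS rule leaves no such room, because 0–1 versus 2–6 can only classify a score on the 0–6 scale.
- A reader might count 11 × 3 + 10 × 3 = 63 tests and 63 × 0.05 ≈ 3 false positives. The article gives measurement times but does not say that every score is tested at every visit.

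**Conclusion.** The point holds as an efficiency fault and a mismatch with the objective. As fixed in the article, the GIS analysis does not measure relief, and neither questionnaire analysis states any use of baseline.

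For a GIS item, the cut costs about 5–16 points of power when it lies near the middle of the scores and up to about 40 when most patients score above it. Not using baseline costs roughly 2–15 more. These figures rest on assumed effects of 0.8–1 SD, assumed score distributions and baseline correlations of 0.3–0.7, none of which the article gives. The direction is the same in every setting tried. Nothing here shows an excess of false positives, and the primary outcome is untouched.

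**What to change.** In Statistical analysis, replace the two questionnaire sentences. Analyse GIS scores on the full 0–6 scale and SF-36 scores on their full scales by ANCOVA with the baseline score as covariate, or rank ANCOVA if the distribution requires it. Report the adjusted difference between arms with its confidence interval. Keep the 0–1 versus 2–6 percentages by arm as description only.

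Do not swap chi-square for Fisher's exact test as the remedy. The article defines no GIS total and singles out no SF-36 component, so this change does not depend on naming either as a key test.

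The cost is analysis wording, best settled before unblinding; no patients, visits or data are added. The drawback is that the dichotomised percentages lose their formal p-values.
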